# Publication Policy

Following completion of the study, the investigator may publish the results of this research in a scientific journal. The International Committeeof Medical Journal Editors (ICMJE) member journals have adopted a trials-registration policy as a condition for publication. This policy requires that all clinical trials be registered in a public trials registry such as [ClinicalTrials.gov](http://www.clinicaltrials.gov/), which is sponsored by the National Library of Medicine. Other biomedical journals are considering adopting similar policies. It is the responsibility of DMID to register this trial in an acceptable registry. Any clinical trial starting enrollment after 01 July 2005 must be registered either on or before the onset of subject enrollment. For trials that began enrollment prior to this date, the ICMJE member journals will require registration by 13 September 2005 before considering the results of the trial for publication.

The ICMJE defines a clinical trial as any research project that prospectively assigns human subjects to intervention or comparison groups to study the cause-and-effect relationship between a medical intervention and a health outcome.

Appendix

Appendix I: Schedule of events

Schedule of events: Enrollment and each episode of malaria

S=Standard of care

R=Research activity

| Day of Study → | 0 | 1 | 2 | 3 | 7 | 14 | 21 | 28 | Unscheduled visit  (before d28) |
| --- | --- | --- | --- | --- | --- | --- | --- | --- | --- |
| Procedure ↓ |  |  |  |  |  |  |  |  |  |
| Informed consent (enrollment only) | R |  |  |  |  |  |  |  |  |
| History-comprehensive | S | Ra | Ra | Ra | Ra | Ra | Ra | Ra | S |
| History-possible adverse drug events and recent history |  | R | R | R | R | R | R | R | S |
| Questioning about antimalarial drug use | S | R | R | R | R | S | R | R | S |
| Physical examination | S | R | R | R | R | R | R | R | S |
| Neurological examination |  |  |  |  |  |  |  | R |  |
| Finger stick blood sample for malaria smear and hemoglobin. | S | Ra | R | R | R | R | R | R | S |
| Venous blood draw (parasite cryopreservation) | R |  |  |  | Rb | R b | Rb | Rb | Rb |
| CBC, ALT, creatinine | R |  |  |  |  | R |  |  |  |
| Finger stick blood sample for drug levels (r= at one of these time points only, research activity) | rc |  | rc | r | r | r | r | r | Rb |
| Assignment of study treatment group | R |  |  |  |  |  |  |  |  |
| Administration of drug | S | R | R |  |  |  |  |  |  |
| GPS mapping of house and household survey (enrollment only or if participant moves) | R |  |  |  |  |  |  |  |  |

a As clinically indicated. Visits are part of research protocol but investigations of complaints are standard clinical care.

b In cases of parasite density>10,000/mm3

rParticipants randomly assigned to have blood drawn on two of these days

cParticipants asked to return three hours after dose

Schedule of events: Routine visits and unscheduled visits (if malaria is diagnosed at any visit, follow schedule listed above)

|  | Routine visit 0-13b | Unscheduled visitc |
| --- | --- | --- |
| History-comprehensive | R | S |
| Questioning about medication use | R | S |
| Questioning about recent travel and bednet use | R |  |
| Physical examination | R | S |
| Malaria smear | R | S a |
| CBC, ALT, Creatinine, Neurological examination | Visits number 4, 8 and 13 |  |
| Additional evaluations | S a | S a |
| Counseling about next visit | R | R/S |

a As clinically indicated

bSame procedure as premature termination visit

cIf malaria is diagnosed, see schedule for malaria episode

Appendix II: Expected adverse reactions to study drugs

|  | Common adverse effects | Management of adverse effects | Rare adverse effects |
| --- | --- | --- | --- |
| CQ(32) | Pruritis  Nausea  Diarrhea  Dizziness | Repeat dose if vomiting occurs (total of 3 attempts) | None reported except for chronic administration (for weekly prophylaxis or treatment of rheumatoid disease) |
| AS(43) | Dizziness (15%)  Nausea (16%)  Vomiting (11%)  Diarrhea (34%)  Anorexia (1%)  Cannot distinguish these effects from underlying malaria disease | Repeat dose if vomiting occurs (total of 3 attempts) | Decreased reticulocyte count  Slight elevation of transaminase  Anaphylaxis |
| AP (Malarone package insert) | Vomiting (10%)  Pruritis (6%)  Diarrhea (6%)  Elevated transaminases (noted in Thai adults)-resolved spontaneously | Repeat dose if vomiting occurs (total of 3 attempts)  Follow transaminase level. Discontinue enrollment in study if abnormality does not resolve by next treatment episode. | Cutaneous reaction  Seizure and psychotic events (causal relationship not established) |
| AZ (Zithromax package insert) | Diarrhea (2.6%)  Abdominal pain (1.7%)  Vomiting (2.3%)  Nausea (0.4%)  Rash (0.6%) | Repeat dose if vomiting occurs.  Evaluate if rash occurs | Anemia  Leukopenia  Headache  Hyperkinesis  Dizziness  Agitation  Nervousness  Edema  Fever  Fungal superinfection  Cough  Urticaria  conjuctivitis |

Appendix III: Use of normal and abnormal values

Normal values for hematological and biochemical evaluations from healthy children in rural Mozambique (Quinto, et al. Tropical Medicine and International Health submitted, 2006) were used to define abnormalities in hemoglobin, ALT and creatinine.

ALT> 300IU/L is greater than 5 times the upper limit of normal

Creatinine>140 mol/L is greater than 3 times the upper limit of normal.

|  | Grade 1 | Grade 2 | Grade 3 | Grade 4 |
| --- | --- | --- | --- | --- |
| **Hemoglobin for children less than or equal to 3 years of age** | 6.6-6.9 g/dL | 6.0-6.5 g/dL | <6.0 g/dL | Cardiac Failure secondary to anemia or requiring a transfusion |
| **Hemoglobin for children greater than 3 years of age** | 7.6-7.9 g/dL | 7.0-7.5 g/dL | <7.0 g/dL | Cardiac Failure secondary to anemia or requiring a transfusion |
| **ALT (IU/L)** | 75-150 | 151-300 | 301-600 | >600 |
| **Creatinine mol/L** | 50-70 | 70-140 | 141-280 | >280 |

Other laboratory abnormalities will be graded according to the DMID Pediatric Toxicity Tables:

[http://icssc.org/documents/AE%20Manual%202003%20Appendices%20February_06_2003%20final.pdf](http://icssc.org/documents/AE Manual 2003 Appendices February_06_2003 final.pdf). Attached below

|  | Grade 1 | Grade 2 | Grade 3 | Grade 4 |
| --- | --- | --- | --- | --- |
| **Neutrophil count** | 750-1200/mm3 | 400-749/mm3 | 250-399/mm3 | <250/mm3 |

[figure not shown]

[figure not shown]

[figure not shown]

[figure not shown]

Appendix IV; Neurological Examination.

The following represents the minimum components of the scheduled neurological examination.

The neurological examination will include the following three parts:

- - 1. Screening for neurological impairment. Adapted from the ten question survey that has been validated for children in developing countries (60).

1. Compared with other children, does the child have any serious delay in sitting, standing or

walking?

2. Does the child have difficulty seeing, either in the daytime or at night?

3. Does the child appear to have difficulty hearing?

4. When you tell the child to do something, does he/she seem to understand what you are

saying? (Age 3+)

5. Does the child have difficulty in walking or moving his/her arms or does he/she have

weakness and/or stiffness in the arms or legs?

6. Does the child sometimes have fits, become rigid, or lose consciousness?

7. Does the child learn to do things like other children his/her age?

8. Does the child speak at all (can he/she make himself/herself understood in words; can

he/she say any recognizable words)? (After age 14 months)

9. For 3- to 9-year-old children ask: Is the child's speech in any way different from normal

(not clear enough to be understood by people other than his/her immediate family)?

For 2-year-old children ask: Can he/she name at least one object (for example, an animal, a

toy, a cup, a spoon)?

10. Compared with other children his/her age, does the child appear in any way backward,

dull or slow?

- - 1. Motor examination

From (61) with written instructions how to score these activities.

III Physical examination (minimum elements listed below)

- 1. Symmetry of movement and strength.
  2. Reflexes
  3. Age appropriate language based on the Denver Developmental Examination (observed by the clinician):
     - Has words 14-30 months
     - Had at least 5 words 18-30 months
     - Combines words OR names 2 objects/body parts 30-42 months
     - Speaks in understandable sentences 43+months

If the answer to any of the screening questions is yes, the participant will be referred to a pediatrician for a complete evaluation. If the participant falls outside the standard error bar above or there is an abnormality in the physical examination, the evaluation will be repeated within 28 days. If the abnormality persists, the participant will be referred to a pediatrician for a complete evaluation.

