## Clinical Evaluations

*History-comprehensive*

- The medications administered to the child in the past week
- Any underlying medical conditions
- Allergies
- Recent travel history and bed net use

*History-possible adverse drug reactions and interval*

A standardized checklist in the case report form includes symptoms of malaria, as well as most common adverse effects of the drugs being administered.

*Questioning about antimalarial use*

The parent/guardian will be asked if any drugs have been administered to the child in the interval since the last visit. The clinician will then specifically ask about the commonly administered antimalarial drugs.

*Physical examination*

The physical examination includes vital signs (temperature, heart rate, respiratory rate), weight, height and a complete physical examination that focuses on: signs of malaria, signs of non-malaria sources of fever and adverse reactions to the medications.

*Neurological examination*

A basic age-appropriate neurological examination will be conducted at the end of every episode of malaria treatment if the participant is not ill (day 28) and also at visit number 4, 8 and 13. See appendix IV.

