## Sample Size Considerations

In a previous longitudinal study of malaria in this population, we found that the mean annual incidence of malaria was approximately 2.5 episodes per year (59) with a standard deviation of approximately 2. Chloroquine is presently highly effective in treating malaria and has a prolonged prophylactic effect, so we have estimated a mean rate of 1.5 malaria episodes per year with chloroquine alone. We derived the sample size required to detect a decrease in the mean to 1.0 episodes per year assuming a Poisson distribution and using a 2 sided test with alpha= .05/3=.0166. The test size was adjusted to accommodate the 3 treatment versus control comparisons. With the above requirements and for a 2 treatment contrast, 120 subjects with complete observation are required per treatment arm to have 90% power (PASS 2005). To account for migration and other causes of attrition, we will enroll an additional 33% (40 subjects) in each regimen. We will accrue 160 per arm for a total of 640 subjects.

Because of the currently estimated efficacy of chloroquine alone in Malawi (in excess of 95%), we are unlikely to determine differences in initial administration (day 28) efficacy between the treatment arms. Power is limited as all arms should have very few early failures. Rates of anemia (<8 mg/dl) at the end of one year should be available in ~120 subjects per arm. The 95% CI half-width for the difference in anemia rates, calculating the variance with a rate of .2, is approximately .10. Thus, the selected sample size should be informative about larger treatment arm differences in anemia rates.

To determine the population pharmacokinetic curve for chloroquine, we have designed a randomized unbalanced study. All participants will have chloroquine levels determined prior to drug administration, at day 14 and at one additional randomly assigned time point. The assignment will be weighted to increase measurement on day two. Planned Interim Analyses

The DSMB will decide when it would like to conduct the interim analysis. The data to be reviewed at this meeting will include safety and efficacy data.

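### Appendix IV refers on any 'yes', but 'yes' is the healthy answer to four of the ten screening items, so every normally developing child meets the trigger

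*Protocol*

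**What the plan says.** Appendix IV sets out the minimum content of the scheduled neurological examination: a ten-question screen, a motor examination and a physical examination. For the screen it gives one rule covering all ten questions: "If the answer to any of the screening questions is yes, the participant will be referred to a pediatrician for a complete evaluation". The repeat within 28 days before referral applies only to the motor and physical parts; referral on the questionnaire is immediate.

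Four of the questions ask whether the child can do something:

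- Item 4, age 3 and over: "When you tell the child to do something, does he/she seem to understand what you are" saying.
- Item 7, no age limit: "Does the child learn to do things like other children his/her age".
- Item 8, after 14 months: "Does the child speak at all (can he/she make himself/herself understood in words", and so on.
- Item 9, version for age 2: "For 2-year-old children ask: Can he/she name at least one object".

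The remaining items (1, 2, 3, 5, 6, 10, and item 9 for ages 3 to 9) ask whether there is a difficulty, delay or difference.

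The Clinical Evaluations section gives the timing of the examination: "end of every episode of malaria treatment if the participant is not ill (day 28) and also at visit number 4, 8 and 13". Secondary Outcome Measures lists neurological examination as a safety outcome, with artemisinin derivatives as the reason. The Final Analysis Plan compares neurological toxicity between arms.

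**The concern.** A rule that refers on any 'yes' works only if 'yes' is the abnormal answer to every question. Here it is the healthy answer to up to three questions per child, depending on age. Followed as written, the rule sends healthy children for a complete pediatric evaluation. It also attaches no consequence of its own to the answer that should cause worry: a child who does not understand, does not learn like others, does not speak or cannot name an object.

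What is at stake is the usefulness of a safety screen. If every healthy child is positive, a positive result carries no information and the referral loses its purpose. If staff set the wording aside, each departure is noncompliance with the protocol, which the Protocol Deviations section classes as a deviation reportable within 5 working days of identification. How staff reinterpret the rule could also vary from one clinician to the next in an open-label trial.

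**Working it through.** **Step 1: direction of each item against the rule.**

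| Item | Asked of | Abnormal answer | Does 'yes' flag a problem? |
|---|---|---|---|
| 1, 2, 3, 5, 6, 10 | all ages | yes | yes |
| 9, ages 3–9 version | age 3+ | yes | yes |
| 4 | age 3+ | no | no, reversed |
| 7 | all ages | no | no, reversed |
| 8 | after 14 months | no | no, reversed |
| 9, age-2 version | age 2 | no | no, reversed |

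Appendix IV gives no scoring key, exception or reverse-scoring note for the questions. By contrast, it says the motor part has written scoring instructions, and the physical part is triggered by an abnormality.

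**Step 2: items to which a healthy child answers 'yes', by age.** Enrolment covers ages over 6 months to 5 years (Subject Inclusion Criteria).

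| Age at examination | Healthy 'yes' items | Count |
|---|---|---|
| 6 to 14 months | 7 | 1 |
| 14 months to under 2 years | 7, 8 | 2 |
| 2 years | 7, 8, 9 | 3 |
| 3 years and over | 4, 7, 8 | 3 |

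The count is at least 1 at every age, and one 'yes' is enough. So the trigger is met by every normally developing child at every examination.

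**Step 3: the opposite error.** A 'no' to a reversed item does not itself cause referral. Such a child is usually still referred because some other item is answered 'yes'. The questionnaire misses a child outright only when all applicable reversed items and all problem items are answered 'no'. This is most plausible at 6 to 14 months, where item 7 is the only reversed item. The clinician-observed language milestones do not help at that age, since the first is "Has words 14-30 months".

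**Step 4: number of screens affected on a literal reading.** Per child, count the first day 28 plus visits 4, 8 and 13, which is 4 examinations.

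- Planned completers: Sample Size Considerations states that "120 subjects with complete observation are required per treatment arm"; 4 arms × 120 = 480.
- Screens among completers: 480 × 4 = 1,920.
- Screens if all 640 enrolled children are retained: 640 × 4 = 2,560.
- Day-28 examinations after later episodes, at the planning rates of 1.0 to 1.5 episodes per year: 480 × 1.0 = 480 to 480 × 1.5 = 720. This is an upper figure, because a child who is ill on day 28 is not examined and some of these dates may coincide with visits 4, 8 or 13.

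The protocol gives no expected number of referrals to compare with these.

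**The case against.** The strongest reply is that this is a slip of wording. The items are headed as a screen for impairment and adapted from a validated questionnaire, so 'yes' most plausibly means a positive screen, and no clinician would refer a child for being able to name an object. That may well describe practice, but the protocol does not say it, and a safety rule should not depend on each reader correcting it.

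Several narrower points stand:

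- The items closest to the animal neurotoxicity findings (hearing, movement and weakness, fits) are keyed correctly. The miskeyed ones concern understanding, learning and speech.
- Item 10 is close to the reverse of item 7 and has no age limit, so a parent worried about learning would often trigger referral there. The risk of an outright miss is small.
- The motor examination and the checks of symmetry, strength and reflexes have their own route to referral, with no lower age limit stated in the appendix.
- Reasons for Withdrawal and Halting Rules do not mention a positive screen, and the Final Analysis Plan does not define neurological toxicity by it. The rule is the same in all four arms.
- The counts in the working are examinations, not harm. They become referrals only if staff follow the text literally. The 480 is the number required for power, not a forecast, and it leaves out examinations of children who drop out.

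These points limit the consequence. They do not make the rule correct.

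**Conclusion.** The rule is wrong as written and should be corrected. It refers every normally developing child at every examination and gives the abnormal answer to items 4, 7, 8 and 9 (age 2) no effect of its own.

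The size is about 1,920 screens among planned completers and up to 2,560 at full retention, plus at most about 480 to 720 among completers after later episodes. These figures assume that the text is followed literally, that the scheduled examinations take place, and that essentially all the children screened are developing normally. The error is mainly over-referral; outright misses should be uncommon and are most plausible at 6 to 14 months.

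Whether the between-arm comparison of neurological toxicity is affected depends on how screen results feed into it, which the protocol does not define. The primary endpoint and the sample size are not affected.

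**What to change.** In Appendix IV, make the trigger any abnormal answer to a screening question, and state the abnormal answer for each item:

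- 'No' is abnormal for items 4, 7 and 8, and for item 9 at age 2.
- 'Yes' is abnormal for items 1, 2, 3, 5, 6 and 10, and for item 9 at ages 3 to 9.

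Print the same key on the case report form, and use it wherever screen results contribute to the neurological safety outcome. The cost is one sentence and a form key. It needs no extra visits or tests, and it means fewer referrals than the present wording requires.
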